The Alcohol Use Disorders Identification Test (AUDIT: Saunders et al. 1993) is normally used as a screening test for alcohol use disorders. However in this context the AUDIT will be used as a means of establishing the severity of alcohol use disorders at baseline, in a way that is least intrusive to naturalistic aim of the trial in the AED setting, and as a means of measuring the adequacy of matching between the intervention groups at baseline. The AUDIT contains 10 items to measure alcohol consumption, alcohol problems and dependence over, in this case, the previous 6 months, and the sum of the item scores provides a measure of severity, which has been used in several previous studies, allowing comparability with other AED samples (Drummond et al., 2005 [ANARP]). We are concerned that the use of more elaborate baseline alcohol consumption measures would interfere with the naturalistic aims of the study and possibly would contribute a form of intervention in themselves, so introducing bias into the evaluation of the interventions by reducing the difference between trial interventions. In addition, participants will complete the Euroqol (EQ5D) as a brief 5 item measure of quality of life. Use of health, social criminal justice services and wider societal costs will be measured via a shortened version of the Service Use Questionnaire (SUQ) which allows estimation of health care and wider social costs for health economic analysis in the six months prior to intervention. A modified version of the Readiness Ruler (LaBrie et al., 2005) will assess participants’ motivational state to change their drinking behaviour.

*Follow-up*

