At 6 and 12 months after intervention, all patients will be contacted either by telephone, or by post, or by email, based on their preference expressed at baseline, by research staff who will be blind to their intervention condition. Patients might also be offered a face-to-face follow-up if preferred. Researchers will administer the shorter Alcohol Use Disorders Identification Test (Extended AUDIT). Alcohol-related problems will be assessed via the brief Alcohol Problems Questionnaire (APQ; Drummond, 1990; Williams & Drummond, 1994). Use of health, social criminal justice services and wider societal costs will be measured with the Service Use Questionnaire (SUQ) which has been used in Primary health care settings (Drummond et al., 2003). This questionnaire allows estimation of health care and wider social costs for health economic analysis in the six months prior to intervention. The Euroqol (EQ5D) will be included as a brief 5 item measure of quality of life, and the modified Readiness to Change ruler will assess motivation to change drinking behaviour.

At follow-up, each patient will also be asked if, and how often, they made use of the Drink-Line telephone number. At 12-month follow up an additional 6-item patient satisfaction questionnaire will also be asked (PSQ) to understand how people felt about the help or advice they received as part of this study.

Economic evaluation

The economic component of the study comprises a cost-effectiveness and cost-utility analysis. The study aims to identify, quantify and value resources related to alcohol SBI by clinicians in AEDs and the subsequent use of health, social care, and criminal justice services by patients following each type of intervention.

Resources utilised in the identification and brief intervention delivery or control condition will be recorded by AED staff (including dedicated AHWs)involved on an ongoing basis. This will allow the calculation of costs related to implementation of different models of screening and brief intervention. Local costs will be used to calculate the costs of the interventions, which will include staff costs, premises costs and costs of leaflets and other consumables. In addition, specific training costs for staff will be calculated, in terms of staff time, premises costs and the cost of training materials.

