Patients’ use of health, social care and criminal justice services will be identified retrospectively using a short form of the Service Use Questionnaire and applying a common set of national unit cost estimates. Patient costs in the 6 month period before SBI can then be compared to cost in the 6 month period after SBI to explore any changes in costs imposed by patients in each group.

The economic analysis will calculate the incremental cost-effectiveness of the control condition with the AHW condition under study, using measures of clinical outcome and quality of life (EQ-5D; The EuroQoL Group, 1990) responses at baseline and at 6 and 12 month follow ups. The use of EQ-5D enables the estimation of Quality Adjusted Life Years. Data will be bootstrapped to account for the expected skewness evident in economic cost data (National Institute for Clinical Excellence, 2004). The analysis will include the construction of cost-effectiveness acceptability curves to illustrate the probability that the brief intervention is more cost-effective than usual care, based on different monetary values being attached to QALYs. The use of QALYs follows the recommendations of NICE(Briggs & Gray, 1999) and enables the value for money afforded by treatment to be compared to a range of other health care interventions. Furthermore, combination of the economic cost data and outcome data with patient data collected in the trial will enable a secondary analysis of various patient characteristics that may influence the cost-effectiveness of the intervention.

Incentives

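### The follow-up Service Use Questionnaire is given the baseline recall window, so as written it yields no post-intervention costs, and costs and QALYs are not tied to one period

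*Protocol*

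**What the plan says.** All places are in the Protocol.

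- **Patient measures, Baseline.** A shortened SUQ is completed before the intervention, "which allows estimation of health care and wider social costs for health economic analysis in the six months prior to intervention".
- **Patient measures, Follow-up.** The contact times are given as follows: "At 6 and 12 months after intervention, all patients will be contacted either by telephone, or by post, or by email". At these contacts, service use and wider costs "will be measured with the Service Use Questionnaire (SUQ) which has been used in Primary health care settings". The text then adds: "This questionnaire allows estimation of health care and wider social costs for health economic analysis in the six months prior to intervention".
- **Economic evaluation, aim.** The study is to value resources used in screening and brief intervention (SBI) and "the subsequent use of health, social care, and criminal justice services by patients following each type of intervention".
- **Economic evaluation, cost comparison.** Service use is identified retrospectively with a short form of the SUQ. The protocol permits a before/after comparison, in which costs over the half-year preceding SBI are "compared to cost in the 6 month period after SBI to explore any changes in costs imposed by patients in each group".
- **Economic evaluation, incremental analysis.** Cost-effectiveness is calculated from clinical outcome and EQ-5D "responses at baseline and at 6 and 12 month follow ups", with QALYs derived from EQ-5D. No period is given for the costs that enter this analysis.

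**The concern.** The recall window is right for the baseline questionnaire and wrong for the follow-up one. A questionnaire given at 6 or 12 months that asks about the half-year before intervention cannot measure what patients used afterwards. A recall period belongs to data collection. If the wrong window reaches the follow-up form, analysis cannot recover the missing service-use data.

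The second part follows from the first. A cost per QALY needs costs and effects over the same period. Effects are drawn from measurements out to 12 months, but no sentence assigns patient service costs to months 7-12, and the one that should do so points to the period before intervention.

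The stake is not marginal to the trial's purpose. Cost-effectiveness is in the study aim and in the first two hypotheses, and the economic section promises QALY-based acceptability curves.

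**Working it through.** The plan gives no figure to reproduce here, so the check sets the stated time windows side by side, with month 0 as the intervention.

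| Item | When given | Period covered, as written |
| --- | --- | --- |
| Baseline short SUQ | month 0 | months -6 to 0 |
| Follow-up SUQ | month 6 | months -6 to 0 |
| Follow-up SUQ | month 12 | months -6 to 0 |
| Before/after cost comparison | not applicable | months -6 to 0 against months 0 to 6 |
| EQ-5D in the incremental analysis | months 0, 6 and 12 | supports QALYs over months 0 to 12 |

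1. *Literal reading of the follow-up SUQ.* At the month-6 interview the stated window lies 6 to 12 months back (6 - 0 = 6; 6 + 6 = 12). At the month-12 interview it lies 12 to 18 months back (12 - 0 = 12; 12 + 6 = 18). Post-intervention months covered by the SUQ: zero.

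2. *Against the economic aim.* The aim is to value service use after each intervention. Zero post-intervention months from the SUQ cannot serve it.

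3. *Against the before/after comparison.* This needs costs for months 0 to 6. Only a month-6 SUQ that looks back over the preceding six months supplies them, which is not the window stated under Follow-up. The two sections cannot both be followed.

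4. *Cost window against effect window.* The longest post-intervention cost window stated is 6 months. The effect measurements run to 12 months. Months 7-12 have effect data and no stated service-cost window.

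5. *With the recall corrected.* Assume that each follow-up SUQ covers the six months before that interview, which the protocol does not say. The month-6 SUQ then covers months 0-6 and the month-12 SUQ months 7-12. Together they span the EQ-5D period with the visits already scheduled.

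The other source of later service use does not close the gap. Under System measures, AED reattendance is taken from computerised records over the 6- and 12-month follow-up. The protocol does not say that these records feed the costing, and they would not show social care, criminal justice or other health service use.

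**The case against.** The best defence is that this is a sentence carried over from the baseline paragraph, not a planned mismatch. The economic section speaks of service use after the intervention with no cut-off at month 6, and the SUQ is scheduled at 12 months, which would be pointless if costs stopped at 6. Once the recall is read sensibly, twelve months of costs can be collected. This stands as an account of what was probably meant. It does not make the sentence correct, and staff who build the form work from what is written.

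It may also be said that the cost horizon of an incremental analysis can be left to an analysis plan, which is not shown. That is fair for the horizon taken alone. It does not cover a recall window that the protocol states, and states wrongly.

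A reader might infer more: that costs are compared only to 6 months, so that the cost-effectiveness ratio sets 6 months of cost against 12 months of QALYs and is biased. The documents do not support this. The before/after comparison is permissive and exploratory, and nowhere is it named as the cost input to the ratio. The incremental analysis states no cost period at all.

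A figure for the share of QALY gain in the uncosted half would also rest on assumption. If a utility gain u builds linearly to month 6 and then holds, the gain is 0.5 × 0.5 × u = 0.25u in the first half-year and 0.5 × u = 0.50u in the second, so 0.50/0.75 = 67% falls in months 7-12. If it instead falls linearly to zero by month 12, each half gives 0.25u and the share is 50%. The protocol gives no basis for choosing between these paths.

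**Conclusion.** The follow-up SUQ sentence is wrong as written. It contradicts the administration of the questionnaire at 6 and 12 months, the aim of valuing later service use, and the comparison with the six months after SBI. This conclusion needs no assumption beyond reading the sections together.

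The companion point is narrower: the stated windows do not secure costs and QALYs over the same period. Six months is the only post-intervention cost window stated, against effect data to 12 months. This is a gap left by the text, not a mismatch that the protocol prescribes.

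The size and direction of any bias cannot be given. They depend on how the ratio is built and on what happens to costs after month 6, and the documents fix neither. The questionnaire form is not shown, so it may already carry the right recall period. The effect is confined to the economic evaluation; the primary outcome at 6 months and the sample size are untouched.

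**What to change.** 1. Under Patient measures, Follow-up, replace the recall sentence with a statement that each follow-up SUQ covers the six months before that interview: months 0-6 at the first and months 7-12 at the second. Check the follow-up form against this wording.
2. Under Economic evaluation, state that the incremental analysis pairs costs and QALYs over one common horizon of 0-12 months, with costs made up of the intervention cost plus both SUQ periods. Any 6-month result should pair 6-month costs with 6-month QALYs.
3. The exploratory before/after comparison can stay, labelled as separate from the incremental analysis.

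The cost is a wording change in two places and a check of one form. The SUQ and EQ-5D are already given at both follow-up points, so no visit, instrument or patient is added.

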
Study aim

To evaluate the implementation, effectiveness and cost effectiveness of BI delivered by an alcohol health worker aimed at reducing excessive drinking in routine AED care compared to brief advice and a patient information leaflet (PIL) in hazardous and harmful drinkers identified by universal or targeted screening.

Study objectives

- To conduct a pragmatic multicentre cluster randomised controlled trial of screening and brief interventions for hazardous and harmful drinkers in AEDs in three English regions.
- To compare the effectiveness and cost effectiveness of brief advice conducted by AED staff (including dedicated AHWs) (Tier 1) with referral to an alcohol health worker (Tier 2) of patients with hazardous and harmful alcohol consumption identified by targeted opportunistic or universal screening.
- To assess the relative impact of the three implementation strategies on alcohol screening and brief intervention activity in AEDs.
- To identify the attitudinal, practical, skill, resource, and reinforcing factors that predict successful implementation of screening and brief intervention in AEDs.
- To identify the optimal method of alcohol screening in AED.
- To assess the relative impact of the three implementation strategies on uptake of alcohol services, including an alcohol helpline.

Hypotheses

- Brief Lifestyle Counselling intervention by an alcohol health worker for hazardous and harmful drinkers identified by targeted screening is more effective and cost effective than Brief Advice conducted by AED staff (including dedicated AHWs) in the typical AED setting.
- Brief Lifestyle Counselling intervention by and alcohol health worker and Brief Advice by AED staff (including dedicated AHWs) are more effective and cost effective than an information leaflet alone.
- Access to referral to an alcohol health worker results in greater screening and intervention activity than training of AED staff in screening and brief intervention alone.
- Attitudinal, practical, skill, resource, and reinforcing factors predict screening and intervention activity.
- Briefer screening methods result in greater implementation of screening activity than more complex methods.

Setting

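### The economic plan specifies only leaflet versus alcohol health worker, so the brief-advice cost-effectiveness contrasts named in the aim, objective and hypotheses have no stated analysis

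*Protocol*

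**What the plan says.** **What the protocol sets out to answer.** The Study aim is to evaluate the effectiveness and cost-effectiveness of the AHW-delivered intervention "in routine AED care compared to brief advice and a patient information leaflet (PIL) in hazardous and harmful drinkers". The second item under Study objectives reads, in part: "compare the effectiveness and cost effectiveness of brief advice conducted by AED staff (including dedicated AHWs) (Tier 1) with referral to an alcohol health worker". Under Hypotheses, the first states that counselling is more cost-effective than brief advice (in patients found by targeted screening). The second states that counselling and brief advice are both more cost-effective than the leaflet.

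**What the economic plan fixes.** The Economic evaluation section says: "The economic analysis will calculate the incremental cost-effectiveness of the control condition with the AHW condition under study". It specifies no other incremental comparison. The acceptability curves are to show "the probability that the brief intervention is more cost-effective than usual care". That is a two-option comparison, and it names neither the intervention nor the arm that stands for usual care.

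**What the arms contain.** Under Brief intervention implementation conditions, control patients get feedback on their screening result and a leaflet. Brief advice adds up to 5 minutes of structured advice. Counselling patients get the leaflet and the structured advice before leaving the department, then a 20-minute session with the AHW.

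**What is collected.** Resource use is recorded for every type of intervention. EQ-5D is taken at baseline, 6 and 12 months. The Service Use Questionnaire is given at 6 and 12 months, but the Follow-up paragraph says it supports "economic analysis in the six months prior to intervention".

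**The concern.** The arms are cumulative: leaflet, then leaflet plus advice, then leaflet plus advice plus counselling. The policy question, whether an AHW is worth paying for on top of brief advice, is the contrast in the second objective. It is also the one the economic plan leaves out.

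A ratio of counselling to leaflet attributes to the AHW whatever benefit comes from the advice those patients also receive. If advice achieves most of the gain at a small part of the cost, counselling can look acceptable against the leaflet and poor value against advice. A two-option acceptability curve has the same blind spot, because it gives no probability that brief advice is the best of the three.

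At stake are one stated objective and the cost-effectiveness part of two hypotheses. The primary drinking outcome is not affected.

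**Working it through.** **Step 1. Contrasts required and contrasts specified.**

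| Contrast | Required by | In the economic plan? |
|---|---|---|
| Counselling vs leaflet | Study aim, hypothesis 2 | Yes |
| Counselling vs brief advice | Study aim, objective 2, hypothesis 1 | No |
| Brief advice vs leaflet | Hypothesis 2 | No |

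One of the three is specified. The acceptability-curve sentence does not supply counselling versus advice whichever intervention it means, because its comparator is usual care.

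**Step 2. Can the omission mislead?** The protocol gives no unit costs, QALY gains, threshold or ratio, so there is no stated figure to reproduce. Every input below is an assumption chosen for illustration.

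- Cost per patient: leaflet £0, brief advice £20, counselling £100.
- QALY gain over leaflet: counselling 0.010; brief advice (q) varied from 0.002 to 0.010.
- Threshold: £20,000 per QALY.

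Formulas: ratio = (difference in cost) / (difference in QALYs); net benefit over leaflet = 20,000 × QALY gain − cost.

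Counselling vs leaflet: 100 / 0.010 = £10,000 per QALY, whatever q is. Net benefit of counselling: 20,000 × 0.010 − 100 = £100.

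Counselling vs advice: (100 − 20) / (0.010 − q) = 80 / (0.010 − q).

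| q (advice gain) | Share of counselling gain | Counselling vs leaflet | Counselling vs advice | Net benefit: advice / counselling |
|---|---|---|---|---|
| 0.002 | 20% | £10,000 | £10,000 | £20 / £100 |
| 0.005 | 50% | £10,000 | £16,000 | £80 / £100 |
| 0.008 | 80% | £10,000 | £40,000 | £140 / £100 |
| 0.0095 | 95% | £10,000 | £160,000 | £170 / £100 |
| 0.010 | 100% | £10,000 | counselling dominated | £180 / £100 |

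Crossover: 80 / (0.010 − q) = 20,000 gives 0.010 − q = 0.004, so q = 0.006, or 60% of the counselling gain. Below that share both ratios favour counselling. Above it they disagree.

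**Step 3. A second assumed set.** Extra cost over leaflet £10 (advice) and £60 (counselling); QALY gain 0.004 and 0.005. Counselling vs leaflet: 60 / 0.005 = £12,000. Counselling vs advice: (60 − 10) / (0.005 − 0.004) = £50,000. With these costs and the same £20,000 threshold, the crossover is q = 0.005 − 50 / 20,000 = 0.0025, or 50% of the counselling gain. The crossover share depends on the inputs. The disagreement does not come from one choice of numbers.

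**Step 4. The questionnaire window.** The Follow-up wording for the 6- and 12-month questionnaire repeats the baseline description. Taken literally, a questionnaire given 6 or 12 months after intervention would ask about the period before it. The Economic evaluation section shows another intention: it aims to cost service use following each intervention, and says "Patient costs in the 6 month period before SBI can then be compared to cost in the 6 month period after SBI". This looks like wording carried over from baseline and needs correcting.

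**The case against.** The strongest reply is that the plan does not say that leaflet versus AHW is the only comparison. Costs are recorded for each type of intervention and looked at by group, so the other contrasts can be calculated, and a later economic plan may add them. It is also fair to say that counselling versus leaflet is a legitimate contrast, since the second hypothesis asks for it.

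Both points limit the concern without removing it. The missing contrasts are unstated, not impossible, and the leaflet ratio is incomplete, not wrong. But the protocol has not left the comparator open for a later document. It names one, and that one does not match its own second objective.

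A reader might also infer three stronger faults, which the text does not support:

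- *That the bootstrap treats patients as independent and so overstates certainty.* The protocol says only "Data will be bootstrapped to account for the expected skewness evident in economic cost data". It gives no resampling unit, and Planned analysis foresees multi-level modelling for the nested design. The resampling unit is commonly left to an analysis plan.
- *That 6-month costs will be set against 12-month QALYs.* The before-and-after cost comparison is described as exploring changes. It is not stated to be the cost input to the ratio, and service use is collected at both 6 and 12 months.
- *That post-intervention costs are undefined.* The Economic evaluation section names service use after the intervention. Only the Follow-up wording is at fault.

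**Conclusion.** The concern holds as an inconsistency within the protocol. The economic plan specifies one of the three cost-effectiveness contrasts that the aim and hypotheses require, and omits the one named in the second objective. This can be read directly from the text and needs no assumption.

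That the omission would mislead is a possibility, not a certainty. In the main illustration it occurs only when brief advice captures more than about 60% of the counselling QALY gain. That figure rests entirely on assumed costs of £0, £20 and £100, a counselling gain of 0.010 QALY and a £20,000 threshold. At lower shares the planned comparison and the missing one agree.

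The plan should be changed before the economic data are analysed, which also avoids a later choice of comparator made with results in view. The questionnaire wording is a minor correction.

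**What to change.** In Economic evaluation, replace the sentence on incremental cost-effectiveness with text to this effect:

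> Leaflet, brief advice and brief lifestyle counselling will be compared in a fully incremental analysis. The three conditions will be ordered by mean cost, options that are dominated or extendedly dominated will be identified, and incremental ratios will be reported for the remaining options. Counselling versus brief advice and brief advice versus leaflet will be reported in every case. Acceptability curves will show, at each value of a QALY, the probability that each of the three conditions is the most cost-effective.

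Replace the usual-care wording with the name of the arm that is meant.

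In the Follow-up paragraph under Patient measures, state that the Service Use Questionnaire at 6 months and at 12 months each covers the preceding six months. Together they then span the same 12 months as the EQ-5D.

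Cost: protocol and questionnaire wording only. Resource use, service use and EQ-5D are already planned in all three arms, so no new data or patients are needed. The price is a less tidy message: with three departments per arm, counselling versus brief advice may be estimated imprecisely, and the report would have to say so.

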Nine AEDs in three English regions (North East, London, South East) will be recruited to take part in the study. Recruitment will take place with the assistance of the British Association of Accident and Emergency Medicine (BAEM, of which [name] is a Professor of Accident and Emergency Medicine and adviser to BAEM on the management of alcohol misuse). All AEDs in the three regions that do not have current routine alcohol screening and brief intervention facilities will be eligible to participate. AEDs will be selected to provide a range of both urban and rural catchment areas.

Design

AEDs will be randomly allocated to one of three implementation conditions (leaflet, brief advice or brief lifestyle counseling intervention) in a cluster randomized design such that there will be 3 AEDs in each condition. AEDs will be randomized to one of three screening conditions (described below) such that there will be 3 AEDs in each condition (see Table **1**). Patients enrolled in the study will have a baseline research assessment carried out by structured interview, and followed in parallel groups over 6, and 12 months. Outcome assessment will be by face to face or telephone interview conducted by a researcher.

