The sample size calculation is designed to account primarily for intervention level outcomes. Powering the study in this way will also account statistically for appropriate outcomes for screening approach and screening method. The primary outcome for this study is the proportion of patients who consume alcohol within recommended levels at 6 month follow up. Recent meta-analysis (Moyer et al 2002) suggest that the difference between brief intervention and control is of the order 13%, 5% reduction in the control group and 18% in the brief intervention group. In order to detect a difference of this magnitude at the 5% significance level with 80% power, for a 2-sided test, requires 109 patients in each of the 3 groups, a total of 327. Our experience with other multi-centre randomized controlled trials of interventions for alcohol use disorders suggests that with assiduous follow-up the potential loss to follow-up across groups is of the order 25%. Taking this loss into accounts inflates the sample required to 131 in each group, a total of 393 patients per intervention.

The proposed study involves a cluster design and requires a statistical adjustment to account for any potential cluster effect. The literature, and our previous experience of trials in primary care, suggest an intra-class correlation coefficient of 0.04 is appropriate. Assuming a cluster size of the order 131 patients this inflates the sample size calculation by a factor of 2.7 requiring patients 393 in each group, a total of 1179, with an expectation that at least 882 will be followed up at 6 months.

We propose to recruit 9 AED’s. AED populations will be screened using 1 of 3 screening method groups (3 AED’s in each group) and will receive 1 of 3 intervention (3 AED’s in each group).

Planned analysis

As the study is pragmatic in design, the planned analysis will be by intention to treat. The primary outcome is dichotomous in nature, drinking within or above recommended levels, and will be analysed logistic regression adjusting for all known prognostic factors, data will be presented as odds ratios and their corresponding confidence intervals. Secondary analyses will be undertaken using the appropriate method for the outcomes, controlling where appropriate for intake values and other known prognostic variables using analysis of covariance. Simulations will be undertaken to encompass both screening approach groups and intention to treat analysis will be undertaken on both groups.

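### The economic evaluation names a bootstrap for skewness as its only uncertainty method and makes no provision for AED clustering, with three AEDs per arm

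*Protocol*

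**What the plan says.** The Economic evaluation section gives one method for uncertainty and one reason for it: "Data will be bootstrapped to account for the expected skewness evident in economic cost data". It then promises the main economic output: "The analysis will include the construction of cost-effectiveness acceptability curves to illustrate the probability that the brief intervention is more cost-effective than usual care". The comparison is stated as "The economic analysis will calculate the incremental cost-effectiveness of the control condition with the AHW condition under study". The section does not say what unit is resampled, and it does not mention AED as a level of variation for costs, QALYs, the incremental ratio or the curves.

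The Design section allocates whole AEDs to intervention, "in a cluster randomized design such that there will be 3 AEDs in each condition". Table 1 places one AED in each cell of the 3x3 layout, so the control-versus-AHW comparison rests on three AEDs against three.

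The Sample size calculation section accepts that this matters: "The proposed study involves a cluster design and requires a statistical adjustment to account for any potential cluster effect". It says "an intra-class correlation coefficient of 0.04 is appropriate", but uses that value only to size the trial. Under Planned analysis, multi-level modelling is mentioned for exploring interactions and is not linked to the economic work.

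**The concern.** A bootstrap for skewness deals with the shape of the cost distribution. It does not by itself deal with dependence between patients of the same AED. Here the dependence comes from the design, because the AED is the unit of randomisation. For part of the cost it is also built into the data: intervention and training costs are to be calculated from local staff, premises and materials costs, which patients of one AED share.

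Cost-effectiveness is in the study aim and in the first two hypotheses. If the standard errors of incremental cost and incremental QALY are too small, the acceptability curve is drawn towards 0 or 1 and suggests more certainty about funding an arm than six AEDs can support. An analysis plan could follow the Economic evaluation section to the letter and still resample patients.

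**Working it through.** **The plan's own figure.** The only clustering figure in the protocol is the design effect: "Assuming a cluster size of the order 131 patients this inflates the sample size calculation by a factor of 2.7". With ICC 0.04 and cluster size 131, 1 + (131 − 1) × 0.04 = 6.2, so 2.7 is not reproduced. It would need a cluster size of 1 + 1.7/0.04 = 43.5, or an ICC of 1.7/130 = 0.013. That is a separate matter, and 2.7 is not used below.

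**Inputs.**
- AEDs per arm: 3 (Design, Table 1).
- Patients analysed per AED: 882/9 = 98, the protocol's expected 6-month follow-up; 131 × 0.75 = 98.25 agrees.
- ICC for costs and QALYs: not given. Assumed values are 0.01, 0.02 and 0.04. The last is borrowed from the sample size calculation for the drinking outcome.

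**If patients are resampled individually.** Design effect DE = 1 + 97 × ICC. The standard error is too small by √DE. Coverage of a nominal 95% interval = 2Φ(1.96/√DE) − 1.

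| ICC (assumed) | DE | √DE | Coverage |
|---|---|---|---|
| 0.01 | 1.97 | 1.40 | 84% |
| 0.02 | 2.94 | 1.71 | 75% |
| 0.04 | 4.88 | 2.21 | 63% |

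At an ICC of 0.005 coverage is 89%. With all 131 patients per AED, coverage is 80% at ICC 0.01 and 57% at ICC 0.04.

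A simulation with skewed (lognormal) residuals, three AEDs of 98 per arm, no true difference and 1,000 trials gave coverage of 81% (ICC 0.01) and 61% (ICC 0.04). The bootstrap probability that one arm is better, which is what an acceptability curve plots, fell above 0.95 or below 0.05 in 27% and 48% of trials, against 10% expected.

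**If whole AEDs are resampled.** With k = 3 AEDs per arm, resampling the AED means understates their variance by (k − 1)/k = 2/3. The percentile interval also behaves as if it used 1.96, although only 3 + 3 − 2 = 4 degrees of freedom are available. Approximate coverage is P(|t₄| < 1.96 × √(2/3)) = P(|t₄| < 1.60) = 82%. Simulation gave about 79% to 81% across ICCs of 0.01 to 0.04. Even if the variance factor were fully restored, P(|t₄| < 1.96) = 88%.

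**With small-sample degrees of freedom.** An interval from AED means using t₄ (critical value 2.78) covered 95% to 96% in simulations of 4,000 trials at each of the same three ICCs.

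**The case against.** The strongest objection is that the section is silent rather than wrong. It does not say that patients are resampled individually, and a bootstrap that resamples AEDs, or works in two stages, would fit the sentence. A reader might infer that the economic analysis will ignore clustering. The document does not support that, and the unit of resampling is commonly fixed in an analysis plan, which is not shown here. This part of the objection stands, so the coverage figures for patient-level resampling are conditional.

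A reader might also take 63% as the coverage implied by the protocol's own ICC. That does not follow either. The 0.04 is justified from the literature and primary care trials and sits in a calculation for a binary drinking outcome. Local costing is no argument for clustering of QALYs, which come from EQ-5D. Follow-up service use is valued at national unit costs, which removes price differences between sites from that component. The 98 per AED is a 6-month figure, and no 12-month retention is given.

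The objection does not dispose of the point. The protocol chose to name the method and its reason, and that method is too certain under either reading: patient resampling because it treats patients as independent, AED resampling because three per arm are too few. Deferring the resampling unit to a later plan does not settle this.

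**Conclusion.** The point holds in a limited form. The protocol fixes a bootstrap, justified by skewness alone, as the uncertainty method for a comparison of three AEDs with three, and does not carry into the economic analysis the cluster adjustment that it calls for elsewhere.

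Under patient-level resampling, standard errors would be too small by about 1.4 to 2.2 and coverage would be about 84% to 63%, for assumed ICCs of 0.01 to 0.04 and 98 patients per AED. Under AED-level resampling, coverage would be about 80%, with little dependence on the ICC. It is not established that the analysts intend to resample patients, nor what the ICC for costs or QALYs is. The matter should be settled before the economic analysis begins. It does not affect trial conduct or the primary drinking outcome.

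**What to change.** In the Economic evaluation section, state that incremental costs and QALYs will be estimated jointly with AED as the cluster level, by a bivariate multilevel model or an equivalent cluster-level analysis. Specify small-sample degrees of freedom, about 4 for three versus three AEDs; a random AED effect without that correction is also fragile with so few clusters. Derive the intervals and acceptability curves from this analysis. Keep a bootstrap only as a sensitivity analysis for skewness, and name its resampling unit. Report the estimated ICCs for costs and QALYs.

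The cost is analyst time and less favourable-looking results. Compared with a patient-level interval using 1.96, intervals would be wider by roughly 1.40 × 2.78/1.96 = 2.0 times at ICC 0.01 and 2.21 × 2.78/1.96 = 3.1 times at ICC 0.04, and the acceptability curves would be flatter. No further data collection is needed.
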